### Ethical Considerations

This study, which includes human participant research, was approved by the IRB of the Florida Department of Health (IRB201900697). The informed consent forms, used in this study, provide participants with a description of the study, its qualitative and quantitative measures, potential risks and discomforts, and explicitly ask the patient to voluntarily agree to participate and allow their data to be collected. Study data are deidentified, as all participants are assigned a numerical code. This code follows the format of OC001. Anonymity of all study participants is ensured. No compensation of any sort is offered to human participants. This is stated in the informed consent form. No identification of individual participants is present in any images of this manuscript or in any supplemental material.

## Results

As of March 1, 2024, a total of 2339 participants have been enrolled. Of the 6 UF Health specialty clinics, 335 were from the UF Health Nephrology Clinic, 466 from the UF Health Sleep Clinic, 597 from the UF Health Ophthalmology Clinic, 526 from the UF Health Urology Clinic, 231 from the UF Health Neurology Clinic, and 184 from the UF Health Pre-Surgical Clinic. The participants’ ages ranged from 18 to 99 years, with an average age of 61 (SD 10.25) years. The average weight of all participants is 194 (SD 14.26) lbs. The race distribution was reported to be 266 (11.42%) African American, 51 (2.18%) Asian, 124 (5.30%) Latino, 1818 (77.73%) White, and 80 (2.61%) others.

The KardiaMobile rhythm strip reported 381 abnormal readings, which are pending analysis from a cardiologist. A total of 78 readings were labeled as possible AFib, 159 readings were labeled unclassified, and 49 were unreadable. Additionally, 1573 (67.25%) of participants report not regularly seeing a cardiologist.

## Discussion

A total of 2339 participants across 6 different medical specialty clinics were enrolled in this study. Preliminary findings of the feasibility and accuracy of performing routine cardiac rhythm sampling in patients deemed at high risk for AFib were encouraging, with the average length of patient enrollment being 3:30 (SD 0.5) minutes after informed consent was completed. This time included the participant filling out the site-specific questionnaire. The average length of the single-lead mobile ECG data collection was just 30 (SD 2.5) seconds. Furthermore, when considering feasibility, there were no reports from clinical staff regarding the patient enrollment effort impacting the flow of clinic operations, and 9 of 10 reported satisfaction with the study on clinic operations per medical staff (n=25). Regarding accuracy, the study demonstrated KardiaMobile to have a sensitivity and specificity of 95% and 97%, respectively, for detecting previously undiagnosed AFib. The relatively short time to collect the single-lead ECG along with the accuracy of the technology in detecting AFib suggests that the implementation of routine rhythm sampling with high-risk patients can be used cost-effectively in an outpatient clinic without increasing the time it takes for the patient to be seen by a physician.

The use of a single-lead mobile ECG strip can serve as a low-cost, effective AFib screen for implementation across outpatient clinics attempting to provide increased health care accessibility. A study published in 2022 suggested an “incremental cost-effectiveness ratio of US $57,894 per quality-adjusted life year, meeting the acceptability threshold of US $100,000 per quality-adjusted life year” regarding the cost-effectiveness of single-lead mobile ECGs [26,27]. Additionally, patients can easily purchase this device on their own and measure their ECG signal from the comfort of their own homes. This may allow for more immediate feedback on their heart health and a reduction in costs from clinic visits.

Limitations to the study include the fact that the study was not designed to measure the impact of potential moderators on the outcomes. Additionally, there were limitations related to the relatively high rates of unclassified or unreadable ECG outputs that have been included in the abnormal findings data. Furthermore, the participants were not asked to return for another reading, as these outputs are representative of the device’s effectiveness.

Overall, this study indicates that the use of a mobile ECG at an outpatient clinic to screen for AFib is acceptable, feasible, and, with preliminary measures, a cost-effective means for detecting previously undetected AFib without impeding clinical operations. These findings have broader public health implications, as an effective screening protocol for AFib can provide earlier access to care through the use of relatively low-cost technologies, which could lead to fewer instances of stroke and more timely initiation of medical therapy.

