## Abstract

**Background:**

Single-lead, smartphone-based mobile electrocardiograms (ECGs) have the potential to provide a noninvasive, rapid, and cost-effective means of screening for atrial fibrillation (AFib) in outpatient settings. AFib has been associated with various comorbid diseases that prompt further investigation and screening methodologies for at-risk populations. A simple 30-second sinus rhythm strip from the KardiaMobile ECG (AliveCor) can provide an effective screen for cardiac rhythm abnormalities.

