**Methods:**

Participants were recruited across 6 clinic sites across the University of Florida Health Network: University of Florida Health Nephrology, Sleep Center, Ophthalmology, Urology, Neurology, and Pre-Surgical. Participants, aged 18-99 years, who agreed to partake in the study were given a consent form and completed a questionnaire regarding their past medical history and risk factors for cardiovascular disease. Single-lead, 30-second ECGs were taken by the KardiaMobile ECG device. If patients are found to have newly diagnosed AFib, the attending physician is notified, and a 12-lead ECG or standard ECG equivalent will be ordered.

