**Results:**

As of March 1, 2024, a total of 2339 participants have been enrolled. Of the data collected thus far, the KardiaMobile rhythm strip reported 381 abnormal readings, which are pending analysis from a cardiologist. A total of 78 readings were labeled as possible AFib, 159 readings were labeled unclassified, and 49 were unreadable. Of note, the average age of participants was 61 (SD 10.25) years, and the average self-reported weight was 194 (SD 14.26) pounds. Additionally, 1572 (67.25%) participants report not regularly seeing a cardiologist. Regarding feasibility, the average length of enrolling a patient into the study was 3:30 (SD 0.5) minutes after informed consent was completed, and medical staff across clinic sites (n=25) reported 9 of 10 level of satisfaction with the impact of the screening on clinic flow.

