### Procedure

Upon obtaining informed consent, research assistants will use the KardiaMobile single-lead ECG by AliveCor to obtain an ECG reading. Before conducting the examination or filling out a cardiovascular-specific screening survey, participants will have to consent to the study. Any questions regarding the survey will be answered by study personnel present in the room. The Mobile ECG recording by the KardiaMobile device will take place in the patient waiting room for approximately 30 seconds.

The smartphone single-lead attachment is compatible with the KardiaMobile app, a HIPAA (Health Insurance Portability and Accountability Act)-compliant smartphone phone app that can temporarily save these ECGs. Each ECG recorded from a participant will be saved on the UF Dropbox using a randomly generated number that corresponds with the participants’ medical record numbers.

The UF Dropbox cloud-hosting service will only be accessible to study personnel who require viewing the ECGs in order to assess them. Access to the UF Dropbox requires logging into the UF Health VPN and accessing the site via a password combination containing uppercase letters, lowercase letters, numbers, and punctuation. The KardiaMobile smartphone app requires either a 6-digit password login, fingerprint scan, or face ID to access. ECG recordings will not be permanently stored on the device hosting the recording and will be immediately transferred from the smartphone to the UF Dropbox.

Mobile ECGs will not contain any protected health information, and participants who volunteer to be a part of this research will only be identified by a number that corresponds to the number of persons the study is recruiting. For example, the first study volunteer will have their images labeled as “01” as well as “UF Health Clinic” and will have no personal health identifiers attached to their Mobile ECG recording.

The paper files collected will be stored in a secured holding unit after completion by study participants in accordance with the UF’s IRB guidelines. Upon notification of an irregular finding from the KardiaMobile single-lead device, the treating physician for the participant will be informed by research assistants. If the participant does not have a past medical history of arrhythmia, the physician will decide to order a 12-lead ECG to confirm any suspicion of cardiovascular disease.

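### A mean ECG collection time equal to the nominal 30-second strip is weak evidence of low burden and cannot support the cost and no-delay conclusion

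*Protocol article*

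**What the plan says.** Specific aim 2 has two parts: that rhythm sampling can be used cost-effectively, and that it does not lengthen the time until the patient is seen. Feasibility is a primary measure, planned under Outcome Measures as asking clinic staff how the device affected flow.

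The recording length appears three times before any result. The Abstract (Background) says "A simple 30-second sinus rhythm strip from the KardiaMobile ECG (AliveCor) can provide an effective screen for cardiac rhythm abnormalities". The Abstract (Methods) says "Single-lead, 30-second ECGs were taken by the KardiaMobile ECG device". The Procedure section says that the recording "will take place in the patient waiting room for approximately 30 seconds".

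The Discussion then gives two times. For the ECG: "The average length of the single-lead mobile ECG data collection was just 30 (SD 2.5) seconds". For enrollment: "average length of patient enrollment being 3:30 (SD 0.5) minutes after informed consent was completed", with the addition "This time included the participant filling out the site-specific questionnaire". The inference to Aim 2 opens "The relatively short time to collect the single-lead ECG along with the accuracy of the technology in detecting AFib suggests" and goes on to cost-effective use with no increase in the time to be seen. The Discussion also cites the absence of staff reports of disrupted flow and a 9 of 10 satisfaction figure from 25 medical staff.

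**The concern.** A recording planned to last about 30 seconds and then reported as averaging 30 seconds tells the reader that the recording was made as planned. It says little about what screening asks of a clinic, because the work around the recording (handing over and positioning the device, transferring the file, informing the physician) does not visibly enter the figure. Yet it is offered as an encouraging result and carries half of the stated argument for Aim 2.

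The second time does not fill the gap, because survey and ECG cannot be separated in it. At stake is the conclusion on a primary measure: a reader deciding whether to adopt the screen would take 30 seconds as its burden and accept that patients are not delayed, when neither has been shown.

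**Working it through.** Both times are descriptive summaries without raw data, so neither can be recalculated. The check compares them with the planned recording length and with the steps that the article describes.

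**Inputs**
- Reported ECG collection time: mean 30 s, SD 2.5 s (Discussion).
- Nominal recording length: 30 s (Abstract, Background and Methods); about 30 s (Procedure).
- Reported enrollment time: 3:30 minutes = 210 s, counted after consent, survey included (Abstract, Results; Discussion).
- Enrolled: 2339. Abnormal readings: 381, of which possible AFib 78 (Results). The Discussion counts unclassified and unreadable outputs among the abnormal findings.
- Planned size: about 655 per clinic, six clinics (Participants); 655 for the study (Statistical Analysis).

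**Step 1. Room for handling in the 30 s figure.** Reported mean minus nominal length: 30 − 30 = 0 s. The coefficient of variation is 2.5/30 = 8.3%, so the recordings were not all of identical length, but the spread is centered on the nominal value.

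**Step 2. What 3:30 can tell us.** If the ECG lies within the 210 s, 210 − 30 = 180 s remain for the survey and everything else, and the ECG is 30/210 = 14.3% of the total. The split cannot be recovered. On that assumption, and taking 30 s as the least the ECG step can need, post-consent time for the ECG step lies between 30 s and 210 s. The ratio of these bounds, 210/30 = 7, describes how little is known. It is not the size of an error, because the two intervals have different content.

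**Step 3. Work after the recording.** The Procedure section has files transferred to Dropbox and the treating physician informed of an irregular finding; the flow diagram adds interpretation by a cardiologist. No time is given for any of these. The share of participants affected by notification depends on what triggers it: possible AFib alone gives 78/2339 = 3.3%, and all abnormal readings give 381/2339 = 16.3%, which is an upper figure.

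**Step 4. Time to be seen.** Neither the Results nor the Discussion reports a time from arrival to physician, with or without screening.

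**Step 5. Is prospective timing still possible?** At 655 per clinic, 6 × 655 = 3930 and 3930 − 2339 = 1591 remain. If 655 is the total for the study, enrollment is already 2339 − 655 = 1684 beyond it and no target remains. The two statements need reconciling before the number still to be timed is known.

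**The case against.** The strongest reply is that the 30-second figure is not a constant imposed by the device. The Procedure section says approximately, and the Discussion reports an SD of 2.5 s, so something was observed. That stands: a fixed strip length is an inference that the article does not state, and nominal recording length is the right term. It also means that one cannot say that 30 seconds would have appeared whatever the burden. What remains is that the mean sits exactly on the nominal length and that the start and stop of the interval are not given. Exclusion of set-up is therefore plausible, not documented.

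Second, the survey is a step of the procedure. The Procedure section and the flow diagram call it a screening survey, so 3:30 can be read as the procedure as run, less consent. A reader might infer that it is a pure research burden that routine screening would drop; the article does not say so. If the ECG is inside the 3:30, including the survey overstates the ECG step and so works against the authors' conclusion.

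Third, the clinic-flow conclusion has other support, namely the staff reports, which are the planned feasibility measure, and the language is partly hedged as preliminary. This also stands. But those reports are opinion from 25 people, and the sentence that draws the Aim 2 conclusion cites collection time and accuracy.

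Fourth, recording takes place in the waiting room, so minutes of handling need not delay the physician. This is correct, and it limits the remedy: handling time alone does not test Aim 2.

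Two further readings are tempting and unsupported. One is that the 159 + 49 = 208 unclassified or unreadable readings (208/2339 = 8.9%) were counted as 30-second collections; the article does not say which recordings entered the average. The other is that all 381 abnormal readings led to notification; the trigger is an irregular finding in the Procedure section and newly diagnosed AFib in the Abstract, and these passages should be reconciled.

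**Conclusion.** The point holds as a limit on what the timing data can support. A mean equal to the nominal recording length, with 0 s of visible allowance for handling and no defined interval, is weak evidence of low burden and should not be a premise for the cost or no-delay conclusion. The 3:30 figure is at most an upper bound of 210 s for survey plus ECG, on the unstated assumption that the ECG lies within it. Clinic flow then rests on staff opinion (n=25), and the time named in Aim 2 is not reported.

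A reader might go further and infer that screening is burdensome or that patients were delayed. The documents do not show that either. True screening time is unknown, and how far it departs from 30 s cannot be computed from the article. The matter should be corrected because it affects the conclusion on a primary measure, and correction is cheap.

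**What to change.** **In the Discussion.** Label 30 seconds as the nominal recording length and remove it as support for the cost and no-delay statements. Limit the clinic-flow conclusion, including its repetition in the closing paragraph, to impact as reported by staff.

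**For participants still to be enrolled** (about 1591 under the per-site reading of 655). Record time stamps for three intervals:
- device hand-over to saved result, including any repeat attempts;
- flagged result to physician notified;
- check-in to being seen.

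Base the Aim 2 statement on these. The first two describe burden; only the third bears on delay. Because the study has no control group, a claim of no increase also needs the third interval from visits without screening in the same clinics. Without that, the result should be reported as descriptive.

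**Cost.** A few extra fields on the data sheet, and a reported time that is likely to exceed 30 seconds. Participants already enrolled cannot be timed in retrospect, so the timing result would apply to the later part of enrollment only.

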## Methods

### Participants

For this study, we will recruit approximately 655 participants from each of the selected University of Florida (UF) outpatient specialty clinics. This sample size was specifically chosen as a result of statistical analysis that suggests this study population would indicate a powered study. There is no control group, as this was an observational study. Due to the nature of our enrollment process, which does not require a follow-up visit, we expect a <1% attrition rate, reaching a desired ~655 samples per site based on our power analysis. Study participants will be between the ages of 18 and 99 years.

Eligible participants are any patient visiting the UF Nephrology Clinic, UF Sleep Clinic, UF Neurology Clinic, UF Ophthalmology Clinic, UF Urology Clinic, and UF Pre-Surgical Center. Patients with a history of AFib will not be excluded from the study, as they provide valuable data on potential risk factors and may be prone to AFib recurrence. Participants were only excluded if they were younger than 18 years of age, a leg or hand amputee, a paralyzed person, unable to consent, or unable to read and comprehend English.

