#### Primary Measures

##### Detection Accuracy

The researchers will measure the accuracy of the KardiaMobile ECG device by comparing the resulting ECG phenotype (normal, possible AF, unreadable, unclassified, tachycardia, or bradycardia) to the patients’ actual heart health as determined by the standard 12-lead ECG.

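### The Discussion reports 95% sensitivity and 97% specificity for undiagnosed AFib as demonstrated, although the abnormal readings are still pending and no reference-standard result is reported

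*Protocol article*

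**What the plan says.** Under Detection Accuracy, a primary measure, the device label is to be compared "to the patients’ actual heart health as determined by the standard 12-lead ECG". The Procedure section describes how that reference arises: the treating physician is told of an irregular finding, and "If the participant does not have a past medical history of arrhythmia, the physician will decide to order a 12-lead ECG". It then adds a comparison through the medical record and mentions sensitivity and specificity. Under Participants, "Patients with a history of AFib will not be excluded from the study".

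The Results give the status of the data: "As of March 1, 2024, a total of 2339 participants have been enrolled"; "The KardiaMobile rhythm strip reported 381 abnormal readings, which are pending analysis from a cardiologist"; and "A total of 78 readings were labeled as possible AFib, 159 readings were labeled unclassified, and 49 were unreadable". The Abstract repeats the pending status. The Discussion confirms that the abnormal total takes in the "relatively high rates of unclassified or unreadable ECG outputs that have been included in the abnormal findings data".

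The same Discussion says that "the study demonstrated KardiaMobile to have a sensitivity and specificity of 95% and 97%, respectively, for detecting previously undiagnosed AFib". Its next sentence combines this accuracy with the short recording time to conclude that routine sampling can be cost-effective. The closing paragraph extends that conclusion to public health.

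**The concern.** Sensitivity and specificity need a reference result for each person in the table. By the article's own account the abnormal readings had not been adjudicated at the data cut, and it shows nothing from the 12-lead ECG that defines accuracy. The Discussion nevertheless gives a point estimate for a primary measure, says it was demonstrated, and names a target condition (previously undiagnosed AFib) that is narrower than the enrolled population.

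A reader could take 95% and 97% as field evidence from more than two thousand outpatients and use it to plan screening. Nothing in the article shows how many people, or how many AFib cases, stand behind the two figures. The sensitivity is the more exposed of the two, because the described work-up does not look for missed cases among normal screens.

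**Working it through.** **1. Can the stated pair be reproduced?** Sensitivity = TP/(TP+FN) and specificity = TN/(TN+FP). The article gives none of TP, FN, FP or TN. It gives only device labels (Results):

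- enrolled: 2339
- abnormal: 381, pending
- possible AFib: 78; unclassified: 159; unreadable: 49; together 78 + 159 + 49 = 286
- abnormal but not broken down: 381 − 286 = 95
- not abnormal: 2339 − 381 = 1958

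This reads the 78 as part of the 381 and takes one reading per participant. The labels fix at most the margin TP + FP = 78, if possible AFib is the positive result. They do not divide that margin into true and false, and say nothing about FN. The 95% and 97% cannot be derived from them.

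**2. Would the described work-up yield the missing cells?**

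| Group | Route to a 12-lead ECG in the Procedure section |
|---|---|
| Irregular finding, no prior arrhythmia | Yes, by the physician's decision |
| Irregular finding, prior arrhythmia | None described |
| Normal screen (most of the 1958 or all of them) | None described |

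False negatives among normal screens are thus not observed against the stated reference. The medical-record comparison might supply some, but it is a different reference from the one under Detection Accuracy, and no result from it is given.

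**3. Illustration: what would the pair rest on if everyone were in the table?** Assume N = 2339, all 78 possible-AFib readings positive, and everyone else negative. List the whole-number tables with TP + FP = 78, TN = 2339 − 78 − FN, sensitivity in [0.945, 0.955) and specificity in [0.965, 0.975). There are three:

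| TP | FN | FP | TN | Sensitivity | Specificity | PPV = TP/78 |
|---|---|---|---|---|---|---|
| 18 | 1 | 60 | 2260 | 18/19 = 94.7% | 2260/2320 = 97.4% | 23.1% |
| 19 | 1 | 59 | 2260 | 19/20 = 95.0% | 2260/2319 = 97.5% (0.9746) | 24.4% |
| 20 | 1 | 58 | 2260 | 20/21 = 95.2% | 2260/2318 = 97.5% (0.97498) | 25.6% |

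Each table holds 19 to 21 AFib cases and a single missed case. The exact (Clopper–Pearson) 95% interval for 20/21 is 76% to 100%.

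**4. How far does that depend on the denominator?** Suppose instead that the table held only 381 people, with the same 78 positives. The tables that fit have TP 69 or 70, FN 4 and FP 9 or 8, so PPV is 69/78 = 88% to 70/78 = 90%. The same stated pair is compatible with a PPV near one quarter or near nine tenths. The article does not say which denominator, if either, was used.

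**The case against.** The strongest reply is that pending describes the cardiologist's reading of the strip, whereas the reference is the 12-lead ECG. Under the Procedure section the treating physician can order a 12-lead without waiting for that reading, and the medical record offers a second source. Detection Accuracy also lists normal among the labels to be compared. A verified table may therefore exist. That stands: one cannot say that no such table is possible, or that no participant with a normal screen had a reference ECG. It does not rescue the sentence, because no such table, subset or count is reported. The flow diagram in Textbox 1 also places the cardiologist's interpretation before the confirmatory 12-lead, which makes the pending status harder to reconcile with a finished accuracy result.

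It can also be said that the pair appears only in the Discussion, in a paragraph that opens by calling its findings preliminary, and that the cost-effectiveness statement leans on recording time and an external cost study as well. This is fair, and limits how prominent the figure is. It does not turn an unsupported result into a demonstrated one.

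Three stronger readings are tempting and are not supported:

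- A reader might infer from step 3 that about three in four possible-AFib alarms are false. That needs essentially all participants and all 78 positives in the table; step 4 shows the opposite picture for a subset. The 78 may also include known AFib, which is not excluded, while the pair is stated for undiagnosed AFib.
- A reader might infer that the one missed case in step 3 must be someone without a 12-lead. It could be among the other 381 − 78 = 303 abnormal readings, some of whom could be sent for one.
- A reader might count all 381 abnormal readings as AFib-positive and find an implausible prevalence. Nothing in the article treats unclassified, unreadable, tachycardia or bradycardia labels as AFib-positive.

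**Conclusion.** The concern holds as an internal contradiction. The Discussion presents as demonstrated a sensitivity and specificity that the Results do not support and that cannot be reconstructed from anything reported. The sensitivity has the further weakness that the described work-up does not verify normal screens against the 12-lead reference.

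The true accuracy could be better or worse than stated, so no size of error can be given. What can be given is the possible thinness of the evidence: under the all-participants assumption, 19 to 21 cases and an interval of 76% to 100% for 20/21. The implied table and its PPV are illustrations that rest on an unstated denominator and on an unknown split by AFib history. The contradiction depends on neither. Because the closing conclusions draw on the figure, it should be settled before they are relied on.

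**What to change.** Reconcile the Discussion with the Abstract and Results in one of two ways.

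- **If no verified table exists:** withdraw the 95%/97% sentence and the accuracy-based parts of the conclusions in the Discussion, including its closing paragraph. Report only the device label counts for now, with the remaining 95 abnormal readings broken down.
- **If a verified table exists:** report its four cells, the number verified and how they were selected, who had a 12-lead and who was classified from the medical record, how unclassified and unreadable outputs were counted, and the restriction to participants without prior AFib. Give sensitivity, specificity and PPV with exact 95% confidence intervals, and correct the pending statement in the Abstract and Results.

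In either case, say that sensitivity is limited to the verified group if normal screens had no reference result. The first route is a text correction. The second needs a tabulation of data that would already be in hand. Neither needs new participants, but the stated result would be withdrawn or carry visible uncertainty.

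### The 95%/97% accuracy is claimed for previously undiagnosed AFib, but one 30-second strip against a 12-lead ECG can at best speak to AFib rhythm present around the recording

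*Protocol article*

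**What the plan says.** The accuracy claim is in the first paragraph of the Discussion, where the study is said to have demonstrated "sensitivity and specificity of 95% and 97%, respectively, for detecting previously undiagnosed AFib". The closing paragraph of the Discussion again concludes that the device finds AFib that had gone undetected.

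The design behind the claim is as follows.

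- **Index test (Procedure):** a single recording that "will take place in the patient waiting room for approximately 30 seconds".
- **Repeat readings (Discussion, limitations):** "the participants were not asked to return for another reading".
- **Follow-up (Participants):** an "enrollment process, which does not require a follow-up visit".
- **Reference (Detection Accuracy, a primary measure):** the device output is compared with the patient's "actual heart health as determined by the standard 12-lead ECG".
- **Who gets the 12-lead ECG (Procedure and Textbox 1):** it is ordered selectively. The Procedure leaves it to the physician after an irregular strip in a patient without an arrhythmia history. No 12-lead ECG is described after a normal strip.
- **Second comparison (end of Procedure):** screening results are also to be compared with the medical record. Neither its role as a reference nor a time window is given.
- **Status (Results):** the 381 abnormal readings still await a cardiologist.

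**The concern.** The claim and the measurement concern different things. A strip and a 12-lead ECG each show the rhythm while they are being recorded. Whether a person has undiagnosed AFib is a question about the person over time. The two coincide only if the arrhythmia is always present in everyone who has it.

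The difference matters because the Discussion uses the accuracy figure to support routine screening of outpatients and, in its last paragraph, links the findings to fewer strokes. For that argument the relevant quantity is the share of people with undiagnosed AFib whom one strip would flag. A reader could take the stated sensitivity as that share, and the limitations paragraph does not correct this. It covers moderators and unclassified or unreadable outputs, but not AFib that is absent during the strip.

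**Working it through.** **1. Can the stated figure be rebuilt?** Sensitivity = TP/(TP+FN) and specificity = TN/(TN+FP). The article gives none of these four counts and no number of 12-lead ECGs, so 95%/97% cannot be reproduced. It can only be tested for arithmetic possibility. Take the 78 possible-AFib strips (Results) as the positives among all 2339 enrolled, and call the number of AFib cases D. The only tables that round to 95% and 97% are:

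| D | TP | FP | Sensitivity | Specificity |
|---|---|---|---|---|
| 19 | 18 | 60 | 18/19 = 94.7% | 1 − 60/2320 = 97.4% |
| 20 | 19 | 59 | 19/20 = 95.0% | 1 − 59/2319 = 97.5% (97.46%) |
| 21 | 20 | 58 | 20/21 = 95.2% | 1 − 58/2318 = 97.5% (just under) |

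Without the 159 + 49 = 208 unclassified or unreadable strips (n = 2131), D runs from 19 to 22. So the figure is possible, but on this reading it rests on roughly 20 cases.

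**2. What can enter the sensitivity?** A false negative needs a reference that shows AFib when the strip did not. Consider a person with undiagnosed AFib who is in normal rhythm at the visit.

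- If a 12-lead ECG were taken at about the same time, it would be normal too, and the person would count as a true negative.
- If no 12-lead ECG follows a normal strip, as the Procedure implies, the person is never verified.
- The medical record does not already contain a diagnosis that has not been made, and no later look-up is specified.

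On none of these routes is the person counted as missed. The sensitivity therefore concerns, at best, rhythm present around the recording.

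**3. How large could the gap be?** Let f be the share of people with undiagnosed AFib who are in AFib during the strip. **f is an assumption; the article does not give it.** Taking 95% and 97% at face value, and allowing for false flags among those in normal rhythm:

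share flagged = 0.95 f + (1 − 0.97)(1 − f) = 0.95 f + 0.03 (1 − f)

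| f (assumed) | Calculation | Share flagged |
|---|---|---|
| 1.00 | 0.950 + 0 | 95% |
| 0.75 | 0.7125 + 0.0075 | 72% |
| 0.50 | 0.475 + 0.015 | 49% |
| 0.25 | 0.2375 + 0.0225 | 26% |

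Only f = 1 returns the stated sensitivity. The rows show direction and scale and are not estimates.

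**4. Is even the rhythm-level figure secure?** If all positive strips but only a share v of negative ones are verified, apparent sensitivity = Se/(Se + (1 − Se)v). With v = 0 it is 100% whatever the truth. With a true Se of 0.50 and v = 0.05 (both assumed) it is 0.50/(0.50 + 0.025) = 95.2%. This is a separate problem, but it means that 95%/97% should not be restated as an established paired comparison with the 12-lead ECG.

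**The case against.** The best defence has four parts.

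- **A medical record is not a snapshot.** The Procedure plans a comparison with it, so the source of the 95% is not certain. That stands as far as it goes. But with no role and no time window the record cannot be credited with capturing AFib that was absent at the visit.
- **The article names its reference.** The Detection Accuracy text says what determines heart health, and the article elsewhere speaks of rhythm sampling and a prescreen. True, but the Discussion sentence drops that qualification and names the condition.
- **The recurrence remark is about known AFib.** The Participants section says that patients with a history of AFib "may be prone to AFib recurrence". A reader might take this as the article's own evidence that undiagnosed AFib is intermittent. It is not, and nothing in the article bounds f.
- **Paired 12-lead ECGs are not described for everyone.** It is therefore not documented that people in normal rhythm were found normal on both tests.

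Two stronger readings are tempting and are not supported. First, that 95% is an upper limit for person-level sensitivity: this needs 95% to be a sound same-moment estimate, which the selective 12-lead ECGs and pending reviews do not establish. Second, that the article overstates how many undiagnosed people were found, or that a given number was missed. It reports no number found. Applying the undiagnosed rates cited in the Introduction to all 2339 participants would import figures from other populations into a sample that includes known AFib.

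**Conclusion.** The accuracy claim is wrong as worded. The design supports, at best, a statement about AFib rhythm present around the time of recording. It does not measure sensitivity for previously undiagnosed AFib. This would remain so if every participant had a simultaneous, blinded 12-lead ECG, so it is distinct from the verification problem.

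The size of the gap cannot be computed from the article. It is nil only if every undiagnosed person is in AFib during those 30 seconds. The 26% to 72% range rests on an assumed f of 0.25 to 0.75 and on accepting 95%/97% as they stand. The conclusion does not rest on any particular f. It rests on the single strip, the absence of repeat readings and follow-up, and the choice of reference.

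**What to change.** - **Detection Accuracy:** replace the wording that equates the 12-lead ECG with the state of the patient's heart by *rhythm on the 12-lead ECG*, and define the measure as sensitivity and specificity for AFib rhythm present at recording.
- **Discussion, first and last paragraphs:** remove undiagnosed or undetected AFib from the accuracy claim. Limit any sensitivity and specificity to participants who had both the strip and a 12-lead ECG. Label the figures preliminary while the abnormal readings await cardiologist review. Do not carry 95%/97% over as a paired result unless the underlying counts support it.
- **Limitations:** state that AFib absent during the strip is not captured, and that sensitivity for undiagnosed AFib as a condition is not measured.

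The cost is the wording of one outcome, two Discussion paragraphs and one limitation. Restricting the figures to participants with both recordings means retabulating data already held; no new data are needed.
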